#### Primary objectives

The two primary objectives are to compare the effectiveness of IPTp-SP with or without screen-and-treat with DP at first antenatal care contact in treating and preventing MIP and to describe the safety profiles of IPTp-SP and IPTp-SP+ including incidence of maternal and perinatal/infant adverse events until 1 year post-partum.

#### Secondary objectives

The secondary objectives include assessment of the relative efficacies of IPTp-SP vs. IPT-SP+ in reducing maternal anemia, improving perinatal outcomes, and preventing placental and congenital malaria. We will also compare the relative impacts of IPTp-SP and IPTp-SP+ on parasite allele frequencies and haplotypes of SP and piperaquine resistance makers among those with incident *P. falciparum* infection.

## Methods

### Study design {8}

This is a phase IIIb open-label randomized controlled superiority trial of standard IPTp-SP vs. IPTp-SP plus screen-and-treat using DP (IPTp-SP+). Participants randomized to the IPTp-SP arm will receive care according to current national guidelines. Participants who are randomized to the IPTp-SP+ arm will receive standard-of-care with the addition of screen-and-treat using RDT and DP at the first ANC visit.

This study protocol has been formatted following SPIRIT reporting guidelines [17].

### Study site {9}

The trial will take place in Nchelenge District, Luapula Province, Zambia. The district is located in the northern wetlands of Zambia alongside Lake Mweru, an area of hyperendemic malaria [18]. Malaria transmission occurs throughout the year. The predominant vector is *Anopheles funestus* which peaks during the dry season (May-September) while both *An. funestus* and *An. gambiae* are found during the rainy season [19]. The population of the district is estimated to be over 296,000 inhabitants consisting mostly of subsistence farmers and fishermen and women. Nchelenge District has one hospital, Saint Paul’s General Hospital (SPGH), twelve rural health centers, and two health posts. The trial will recruit and follow obstetric patients and their offspring at two of the rural health centers and SPGH. SPGH is equipped with an operation theater and labor-and-delivery ward for the provision of essential obstetric services.

### Study population {10} {15}

Pregnant women in the second and third trimesters attending routine ANC visits at the study health facilities will be systematically screened for potential enrollment. Inclusion and exclusion criteria are listed in Table 2. All volunteer pregnant women presenting to the ANC for the first time of their current pregnancy will be assessed for eligibility according to the following criteria: age ≥15 years, estimated gestational age 16–26 weeks, hemoglobin concentration ≥7 g/dL, ability to provide informed consent, residence in the study area with intention to deliver at the health center, no evidence of clinical malaria or other acute illness, and ability to tolerate oral medication. Women will be deemed ineligible for any of the following: infection with human immunodeficiency virus (HIV) or unknown HIV status, prior IPTp-SP or other antimalarial use or antimicrobials with antimalarial activity during the current pregnancy, intolerance to either of the study drugs, existing or prior obstetric complications, prior enrollment in the study or concurrent enrollment in another study, concurrent medications with potential for drug-drug interactions or potentiation of cardiac arrhythmia, presence of chronic illness or other factor deemed likely to influence the pregnancy outcome, or other reason which is judged by the investigator to render the individual unsuitable for study participation.

**Table 2 Tab2:** Inclusion and exclusion criteria

Inclusion criteria	
• Ability and willingness to provide informed consent^a^	
• Gestational age of 16 to 26 weeks at enrollment	
• Asymptomatic on presentation, with or without a positive RDT test result^b^	
• Age ≥15 years	
• Residence within the study catchment area and no intent to move out of the study catchment area before delivery or to deliver outside of the catchment area	
• Willingness to adhere to all study requirements including to deliver at the health facility	
• Ability to take oral medication	
Exclusion criteria	
• Infection with HIV at enrollment or unknown HIV status^c^	
• History of IPTp-SP or other antimalarial drug use during the current pregnancy	
• History of intolerance or allergic reaction to any of the study drugs	
• History of known pregnancy complications or bad obstetric history including pre-existing illness likely to cause complication of pregnancy such as repeated abortions, stillbirths or eclampsia	
• Hemoglobin concentration <7 g/dL	
• Any significant illness at the time of screening that requires hospitalization, including severe malaria	
• Prior enrollment in the study or concurrent enrollment in another study	
• Treatment with antimicrobials with antimalarial activity within the prior 2 weeks (e.g., clindamycin, azithromycin, tetracycline, clarithromycin, levofloxacin)	
• Concurrent use of medications with potential for drug-drug interaction or potentiation of cardiac arrhythmia^d^	
• History or presence of major illnesses likely to influence pregnancy outcome including hypertension, diabetes mellitus, asthma, epilepsy, renal disease, liver disease, fistula repair, heart disease, or active tuberculosis.	

*HIV*, human immunodeficiency virus; *IPTp-SP*, intermittent preventive treatment with sulfadoxine-pyrimethamine; *RDT*, rapid diagnostic test for *P. falciparum*. ^a^For participants <17 years old, consent will be obtained from the parent or legal guardian and verbal assent will be obtained from the participant. ^b^Asymptomatic defined as absence of fever (temperature <37.5 °C) at baseline and fewer than three of the following symptoms: fever in the past 24 h, headache, weakness/fatigue, myalgia, and arthralgia. ^c^HIV voluntary counseling and testing will be included. We will exclude those on current cotrimoxazole prophylaxis or antiretroviral treatment. ^d^The list of agents includes pentamidine, antiarrhythmic agents (e.g., amiodarone, sotalol), antihistamines (e.g., promethazine), systemic antifungals (ketoconazole, fluconazole, itraconazole), diuretics (e.g., hydrochlorothiazide, furosemide), antipsychotics (haloperidol, thioridazine), antidepressants (imipramine, citalopram, escitalopram), and antiemetics (domperidone, chlorpromazine, ondansetron)

### Randomization and masking {16a} {16b} {16c} {17a} {17b} {23}

The following procedures will be used to ensure an unbiased assessment of treatment safety and efficacy. A computer-generated randomization schedule will be generated by the study statistician prior to the start of the study and kept in a locked cabinet accessible only to the study coordinator who will be responsible for assigning participants to a study treatment arm. The schedule will comprise blocks of varying size to allocate, in a 1:1 ratio, eligible participants to either IPTp-SP or IPTp-SP+. The trial is open-label. However, study investigators, study clinicians, and statisticians are masked to treatment assignment. Investigators will be unmasked after all participants have delivered. A Data and Safety Monitoring Board (DSMB) will be established to review safety data. Statisticians will remain masked until after the DSMB has approved the final analysis plan and the database is locked. All outcome assessors, including laboratory parasitologists and pathologists, will also be masked until the final database is locked.

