### Trial objectives {7} {12}

This research protocol is designed to assess the safety and efficacy of a revised IPTp schedule that incorporates a screen-and-treat strategy using RDT and DP at the first antenatal care visit (IPTp-SP+). The research objectives and corresponding endpoints are listed in Table 1.

**Table 1 Tab1:** Outcomes

Objectives	Outcomes/endpoints
Primary objectives	
To compare the effectiveness of IPTp-SP versus IPTp-SP+ for treating and preventing maternal *P. falciparum* infection To compare the safety and tolerability of IPTp-SP versus IPTp-SP+	• Relative hazard of *P. falciparum* infection diagnosed by PCR at day 42 after randomization (primary outcome) • Relative hazard of *P. falciparum* infection diagnosed by PCR or microscopy at days 14, 28, 35, 42, 63, delivery, and 1-month post-partum in infants • Proportion who experience at least one episode of *P. falciparum* infection by day 14, 28, 35, 42, or 63 • Proportion with treatment or prevention failure at day 42 stratified according to study drug (SP or DP) • Median time to first episode of MIP • Acute, chronic, and prior placental infection at delivery • Medication-related adverse events and serious adverse events until 1-year post-partum (primary outcome)
Secondary objectives	
To compare the effectiveness of IPTp-SP versus IPTp-SP+ for reducing complications of MIP	• Mean birth weight and prevalence of low birth weight (within 72 hours post-partum), neonatal mortality (within 28 days post-partum), congenital malaria diagnosed by PCR, placental malaria diagnosed by histopathology using placental biopsies, maternal anemia (hemoglobin changes at days 14, 28, 42 and 63), congenital anemia, Incidences of pregnancy losses, congenital *P. falciparum* infection
To compare selection for drug resistant parasites between infected individuals in the IPTp-SP and IPTp-SP+ treatment groups	• Relative allele frequencies of genotypic markers of drug resistance in malaria parasites
To measure piperaquine exposure and duration	• Terminal elimination half-life of piperaquine determined by noncompartmental analysis of drug concentrations at 0, 14, 28, 35 and 42 days

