### Clinical procedures {11d} {13} {15} {26a}

Study procedures are outlined in Table 3 and the flow of events is shown in Fig. 1. The informed consent will be administered by a study nurse in the local language (Bemba) and/or in English as preferred by the participant. Assent will be obtained from participants <18 years old, and informed consent will be obtained from those ≥18 or the legally authorized representative for minors. If the participant cannot provide a written signature, then a thumbprint will be obtained. After collection of demographic data, provision of informed consent, baseline medical and obstetric history, and physical examination by a study physician including eligibility assessment, participants will be randomized to either the IPTp-SP or IPTp-SP+ treatment groups. All participants will undergo hemoglobin measurement as part of the screening process. On enrollment, fingerstick blood will be drawn for preparation of dried blood spots (DBS) for subsequent molecular testing. In addition, participants randomized to the experimental group (IPTp-SP+) will undergo RDT.

**Table 3 Tab3:** Schedule of events

	Antenatal period *Study day*									Postpartum period *Study month*			
Event	0	1–2	14	28	35	42	63^a^	Unsch.	Birth	1	6	9	12
Informed consent/oral assent	•												
Medical history	•												
Physical examination, including height, weight, temperature	•		•	•	•	•	•	•	•				
Fetal viability	•		•	•	•	•	•	•	•				
Focused history and examination			•	•	•	•	•	•	•	•	•	•	•
Adverse event evaluation	•	•	•	•	•	•	•	•					
IPTp-SP^b^	•				•		•						
RDT^c^	•												
Treatment with DP^d^	•	•											
DBS for PCR, genotyping	•		•	•	•	•	•	•	•				
Malaria microscopy^e^			•	•	•	•	•	•	•				
Hemoglobin measurement	•		•	•		•	•		•	•			
Blood sample for PK^d^	•		•	•	•	•							
Delivery									•				
Placental biopsy, cord blood									•				
Infant assessment including history and exam, weight, heel stick									•	•	•	•	•

^a^Monthly visits continue until delivery

^b^Includes participants randomized to standard IPTp-SP, participants randomized to IPTp-SP+ who test negative at the first visit, and all participants in both groups at days 35, 63 and then monthly until delivery

^c^Limited to participants randomized to IPTp-SP+

^d^Limited to participants randomized to IPTp-SP+ who test positive by RDT at the first visit

^e^Only participants with signs or symptoms of malaria will undergo microscopy

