### Safety assessments {22}

Drug safety will be monitored at every visit during the course of the study in compliance with International Conference on Harmonization Good Clinical Practice guidelines for adverse events (AEs) and serious adverse events (SAEs) [26]. All expected and unexpected AEs will be collected and reported in trial publications. SAEs will be reported to the sponsor and the ethics committee within 24 working hours of the study staff first becoming aware. Investigators will determine the relationship between safety signals and the study drugs and define outcomes, according to standard classifications [26].

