### Statistical analysis {20a} {20b} {20c}

Longitudinal data will be displayed using the nonparametric Kaplan-Meier estimations of the survival function. The primary analysis will be comparison of the 42-day incidence of MIP using multivariate models to estimate the relative hazard between the IPTp-SP and IPTp-SP+ groups according to intention-to-treat (ITT). Testing for proportionality of hazards will be done using formal statistical testing with Schoenfeld residuals as well as visual inspection of the nonparametric survival estimates. For non-proportional hazards, an extended Cox model will be applied. To handle interval censoring due to participants who miss one or more follow-up visits, we will use parametric models for interval-censored survival-time data. The relative hazard will be estimated in parametric models accounting for recurrent events by using a robust variance estimator. For the primary safety analysis, we will compare the proportions of serious and non-serious AEs using logistic regression models and relative hazards of AEs using Cox regression methods as above. Secondary analyses of continuous outcomes (hemoglobin concentration, birthweight) will be examined in linear regression models and in logistic regression models for binary outcomes (prevalence of low birth weight, neonatal mortality, placental malaria, congenital malaria, maternal anemia, congenital anemia, drug resistance allele frequency). Prespecified subgroup analyses will be done according to the following strata: primigravidae, multigravidae, gestational age at enrollment, delivery before or after the day 63 visit, treatment dose on a mg/kg basis, positive *P. falciparum* PCR on enrollment, and presence or absence of quintuple and sextuple mutations. In a secondary analysis, we will compare the proportions of treatment failures and prevention failures according to the antimalarial drug given at the first encounter (SP or DP) in an on-treatment analysis using logistic regression. Treatment failures will be defined as recurrent infections that are determined by genotyping to be recrudescent parasites from the initial infection in participants who tested positive by PCR at the initial visit. Prevention failures will be defined as PCR-confirmed parasitemia in participants who initially tested negative by PCR at the first visit, or who tested positive by PCR at the first visit but who experienced reinfection with a new parasite as determined by genotyping. No interim analysis is planned. Every effort will be made to collect complete data for all participants and minimize missing data. Missing data will be handled using multiple imputation.

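### Investigators who judge drug-relatedness are unmasked after the last delivery, although the primary safety outcome runs to 1 year post-partum; Table 3 also leaves adverse event evaluation blank from birth on

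*Protocol article*

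**What the plan says.** All references are to the protocol article.

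- **Outcome.** Table 1 (Trial objectives) lists "Medication-related adverse events and serious adverse events until 1-year post-partum (primary outcome". The Primary objectives section gives the scope as "including incidence of maternal and perinatal/infant adverse events until 1 year post-partum".
- **Who judges relatedness.** Under Safety assessments: "Investigators will determine the relationship between safety signals and the study drugs".
- **When masking ends.** Under Randomization and masking: "Investigators will be unmasked after all participants have delivered". The same paragraph adds: "All outcome assessors, including laboratory parasitologists and pathologists, will also be masked until the final database is locked".
- **When AEs are assessed.** The row "Adverse event evaluation" in Table 3 is marked from day 0 through the unscheduled-visit column and is empty at birth and at months 1, 6, 9 and 12. Safety assessments says: "Drug safety will be monitored at every visit during the course of the study". Clinical procedures adds that obstetric complications at delivery are recorded as AEs, and that infants are seen at months 1, 6, 9 and 12 with an interval medication and hospitalization history.
- **What is compared.** Under Statistical analysis, for the primary safety analysis: "we will compare the proportions of serious and non-serious AEs using logistic regression models", together with Cox models for AEs. No restriction to drug-related events is stated.

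**The concern.** Attribution of an event to a study drug is a judgment, and knowing the arm can sway it. Here that judgment helps define a primary outcome, and the people named as making it lose their masking before the outcome's window closes. The masking section presents its procedures as protecting the assessment of safety as well as efficacy, so the early unmasking works against its own purpose.

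Two further mismatches touch the same outcome. The visit schedule shows no AE evaluation in any column from birth onward, which is the whole post-partum part of a 1-year horizon. And the outcome named in Table 1 (medication-related) is not the quantity the analysis section compares (all serious and non-serious AEs).

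**Working it through.** **1. Masking against the outcome window.** Relatedness is assigned to investigators. Investigators have their own unmasking time, the last delivery. The outcome runs 1 year beyond each delivery. So every infant born within a year before the last delivery has some follow-up after unmasking.

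**2. How much follow-up that is.** The article gives no figure to reproduce, so this is a sizing exercise.

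Inputs from the article: recruitment from 22 April 2019 to 19 June 2020 = 424 days (Trial status); entry at 16-26 weeks (Table 2).
Assumptions: uniform accrual; uniform gestational age at entry; delivery at 40 weeks; every infant followed for 365 days; unmasking at the latest expected delivery.

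- Enrolment day E is uniform on 0 to 424. Time to delivery T = 7 × (40 − gestational age) runs from 98 to 168 days, mean 133.
- Latest delivery: day 424 + 168 = 592, i.e. 4 December 2020.
- Delivery day D = E + T. Follow-up extends past unmasking if D + 365 > 592, i.e. D > 227.
- P(D ≤ 227) = (227 − 133)/424 = 0.222, so **about 78%** of infants have some follow-up, including the month-12 visit, after unmasking.
- Person-time: for given T, the mean number of days after unmasking is (197 + T)²/(2 × 424). Averaged over T: (330² + 70²/12)/848 = 109,308/848 = 128.9 days. 128.9/365 = 0.353, **about 35%**.
- Month-9 visits (9 × 30.4 = 273.6 days): 1 − (592 − 273.6 − 133)/424 = 0.56.
- Month-6 visits (6 × 30.4 = 182.4 days): 1 − (592 − 182.4 − 133)/424 = 0.35.
- Month-1 visits: about 2% by simulation.

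Sensitivity, with unmasking held at 4 December 2020:

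| Entry (weeks) | Infants with follow-up after unmasking | Person-time after unmasking |
|---|---|---|
| 16-26 | 78% | 35% |
| 16-20 | 83% | 40% |
| 22-26 | 73% | 31% |

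An earlier last delivery raises every share. If the last woman enrolled had entered at 26 weeks, she would deliver about 25 September 2020. Unmasking on that date gives 51% of person-time and 94% of month-12 visits under 16-26 week entry. That is an outer illustration only, since under those entry assumptions some women would still be pregnant.

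**3. Table 3.** The table has 13 columns: days 0, 1-2, 14, 28, 35, 42 and 63, unscheduled, birth, and months 1, 6, 9 and 12. The AE row is marked in 8 and blank in the last 5. Other rows (focused history and examination, infant assessment) are marked in those same 5 columns, so the blanks are not an effect of text extraction. They contradict the every-visit statement, the recording of obstetric complications as AEs at delivery, and the 1-year horizon of Table 1.

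**4. Outcome against analysis.** Table 1 applies a relatedness filter, at least to AEs. The analysis section states none. If that comparison is run as written, relatedness does not enter it.

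**The case against.** **The primary comparison does not use relatedness.** A reader might infer that early unmasking biases the primary safety analysis. The documents do not support that: the stated comparison counts all serious and non-serious AEs by arm. Table 1 can also be parsed as medication-related AEs plus all SAEs, which narrows the part that depends on judgment. This stands. The exposure is to the outcome as Table 1 names it, and the mismatch between the two places remains.

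**Outcome assessors stay masked to database lock.** That sentence is not limited to laboratory staff and could be read to cover those who judge AEs. But relatedness is given to investigators by name, and investigators have a separate, earlier unmasking time. At best the section gives two times for the same task. Quarterly review by the safety monitoring board does not change who makes the judgment.

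**Post-partum events are plainly meant to be collected.** A reader might infer from Table 3 that events after birth would be picked up only by chance. The every-visit statement, the delivery procedures, the infant hospitalization history and the history and examination marks in Table 3 all point the other way. The blank row is an internal contradiction, not evidence that events go unrecorded.

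**The 78% is the largest available measure.** It counts any infant with any follow-up left. The person-time share of about 35% describes the exposure better, and the article does not show how many relatedness calls would arise at 6 to 12 months. This stands.

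**Clinician masking.** A reader might also infer that clinicians described as masked cannot be, given the open-label drugs. That is inference. Allocation sits with the study coordinator, DP dosing is observed by a nurse or community health worker, and the medication history at visits is not said to reveal the study drug. The point here does not rely on it.

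**Conclusion.** The concern holds in a limited form. Investigators who judge drug-relatedness are unmasked before the 1-year window of a primary outcome closes, with about 35% of infant person-time (31-40%) and about 78% of month-12 visits (73-83%) still ahead. These figures rest on uniform accrual, delivery at 40 weeks and unmasking on about 4 December 2020. The number of affected judgments, and the direction of any bias, cannot be derived from the article.

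The all-AE comparison by arm is untouched by this route, but it is not the outcome Table 1 names. Table 3 contradicts the text on AE evaluation from birth on and needs to be reconciled with it.

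**What to change.** 1. **Masking section.** State one unmasking time for everyone who judges AE relatedness: database lock after the last month-12 visit. Cost: investigators see unmasked data up to a year later.
2. **If investigators have already been unmasked.** The article says only that data collection is ongoing, so this is possible. Report which relatedness judgments were made after unmasking, and rely on the all-cause AE/SAE comparison by randomised arm that the analysis section already plans.
3. **Table 3.** Mark AE/SAE evaluation at birth and at months 1, 6, 9 and 12, so that it agrees with Table 1, Clinical procedures and Safety assessments. Cost: a schedule correction, since visits with history and examination are already planned there.
4. **Table 1.** Align the safety outcome's wording with the comparison in Statistical analysis. This is more than editing: recruitment closed on 19 June 2020, and changing the wording of a stated primary outcome needs a dated amendment with reasons, submitted to the ethics committee as the article requires for any amendment.

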### Quality assurance and data and safety monitoring board {21a} {23}

Four site visits will be conducted by an independent external monitor who will carry out a minimum of 20% source data verification. A data and safety monitoring board (DSMB) composed of four members will be established. The DSMB will meet quarterly to review progress and provide independent assessments of the quality of the data produced and the safety of study treatments.

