## Trial status

This is protocol version 2.2 dated 28 October 2019. Recruitment began on 22 April 2019 and ended on 19 June 2020 with data collection still ongoing. This protocol was not submitted for publication during the active enrollment period due to delays caused by the coronavirus pandemic and medical emergency with prolonged recovery of one of our senior team members.

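### Investigators are unmasked at the last delivery, about a year before database lock is possible, but the final analysis plan need not be approved by then

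*Protocol article*

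**What the plan says.** The Randomization and masking section describes an open-label trial but adds a masking rule: "However, study investigators, study clinicians, and statisticians are masked to treatment assignment". It then gives three release points:

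- Investigators: "Investigators will be unmasked after all participants have delivered".
- Statisticians: "Statisticians will remain masked until after the DSMB has approved the final analysis plan and the database is locked".
- Outcome assessors: "All outcome assessors, including laboratory parasitologists and pathologists, will also be masked until the final database is locked".

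Approval of the analysis plan appears only in the rule for statisticians. There it is one of two conditions, alongside database lock, and the text puts the two in no order.

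Other sections set the calendar. Clinical procedures and Table 3 schedule infant visits up to 12 months post-partum. Table 1 runs the primary safety outcome to one year post-partum. Data management puts the final lock after all queries are resolved. Trial status says: "Recruitment began on 22 April 2019 and ended on 19 June 2020 with data collection still ongoing".

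Statistical analysis defines the primary efficacy comparison as 42-day incidence, expressed as a relative hazard, by intention to treat. The model is described only as multivariate, with no covariates named. The section then mentions an extended Cox model, parametric interval-censored models and a recurrent-event analysis with robust variance.

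**The concern.** A prespecified analysis is protected only if nobody who can shape it knows the allocation while choices remain. Here the investigators learn the allocation at a point unrelated to the plan's approval. They are not distant from the analysis. The Administrative information table says they designed and revised the protocol, and under Data management they check the case report forms and database throughout data collection. By the last delivery every day-42 sample should have been taken.

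If an open choice about the primary model were settled after that, with results by arm in view, it could follow the result, and the nominal 5% two-sided error would not cover it. Even if nothing of the kind happened, the stated sequence would not let the trial team show that it had not.

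**Working it through.** The protocol gives no figure to reproduce on this point. The check is the order of events, followed by the possible size of the effect.

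**1. Length of the gap.** Inputs from the documents: recruitment ended on 19 June 2020 (Trial status); entry at 16 to 26 weeks' gestation (Table 2); primary efficacy outcome at day 42 (Table 1); last infant visit at 12 months (Table 3). Assumption: delivery at 37 to 42 weeks.

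- Day 42 of a woman enrolled on the last day: 19 June 2020 + 42 days = 31 July 2020.
- Earliest last delivery: 37 − 26 = 11 weeks after 19 June 2020 = 4 September 2020.
- Latest last delivery: 42 − 16 = 26 weeks after 19 June 2020 = 18 December 2020.
- Last 12-month infant visit: 4 September to 18 December 2021.

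The last day-42 sample is therefore due 5 to 20 weeks before investigators are unmasked (11 − 6 and 26 − 6 weeks). The protocol describes one final lock, and it cannot precede the last infant visit. The gap from investigator unmasking to lock is at least about 12 months at either end of the range.

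**2. Who knows the arms in the gap.**

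| Group | Masked until | Plan approved first? |
|---|---|---|
| Investigators | last delivery | not required |
| Statisticians | plan approved and database locked | required |
| Outcome assessors | database lock | not stated |

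**3. What is still open.** Fixed: 42-day incidence, relative hazard, intention to treat, a list of subgroups, no interim analysis. Partly fixed: the extended Cox model applies if hazards are not proportional, and the interval-censored models apply when visits are missed. Not settled in this document: the covariates, and whether the primary relative hazard counts first or recurrent infections.

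**4. Possible size.** Null simulation, all inputs assumed apart from the 162 per arm in Sample size calculation: 24% PCR-positive at entry, about 22% 42-day incidence, PCR at days 14, 28, 35 and 42 with persistence of infection, 6000 runs. Each single test rejected in 4.6 to 5.1% of runs.

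- Smallest p-value of three readings (first-event log-rank, any infection by day 42, recurrent count with robust variance): 7.1%.
- Smallest of four, adding adjustment for enrolment PCR: 8.4%.

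A second, separately written simulation (4000 runs, about 19% 42-day incidence) gave 4.3 to 5.1% for single tests, 7.1% for the best of three and 8.3% for the best of four. Monte Carlo standard error at 7.1% is √(0.071 × 0.929 / 6000) = 0.003 for the first and √(0.071 × 0.929 / 4000) = 0.004 for the second, so the two agree.

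The set of readings is generous. The log-rank test stands in for the hazard model and is not named in the protocol, and any infection by day 42 is a proportion rather than a hazard.

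**The case against.** The strongest reply is that the people who run the analysis and read the samples are protected. Statisticians stay masked until both conditions are met, and parasitologists and pathologists stay masked to lock. Nothing in the document says that investigators write the plan; approval lies with the data and safety monitoring board. The main frame of the primary analysis is fixed, the plan itself is not shown, and it may have been final well before the last delivery.

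Most of this stands, and it limits the point to choices still open. It does not remove the point, because the release rule is stated in this document and permits approval after investigators are unmasked. A plan written under that rule could carry either date. The masking of statisticians is also a little weaker than it looks: "A computer-generated randomization schedule will be generated by the study statistician prior to the start of the study", although the schedule is then locked away with access for the coordinator only.

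Three stronger readings are tempting, and the documents do not support them.

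- A reader might infer that the monitoring board is unfit to approve the plan because it has seen results by arm. The text says only "A Data and Safety Monitoring Board (DSMB) will be established to review safety data" and "The DSMB will meet quarterly to review progress and provide independent assessments of the quality of the data produced and the safety of study treatments". Access by arm is not stated, and no interim analysis is planned.
- A reader might infer that the plan only has to be approved before lock. The text sets no order between approval and lock.
- A reader might quote a larger error rate. Taking the best of six readings gave 13.1% and 14.8% in the two simulations, but that set adds a day-42 snapshot and an analysis of baseline-negative women only. The first is hard to square with a relative hazard for 42-day incidence, and the second departs from intention to treat.

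It can also be said that early unmasking bears more directly on safety, since under Safety assessments investigators judge drug-relatedness while infants are still followed. That is fair, but it is a separate matter that dating the plan would not cure.

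**Conclusion.** The point holds in a limited form. The protocol lets investigators know the arms for about 12 months before lock is possible, and it does not require the analysis plan to be final before that period begins. The length of the gap follows from the infant follow-up schedule and a single final lock. Only the calendar position, September to December 2020 for the last delivery, depends on the assumption of delivery at 37 to 42 weeks.

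It would be wrong to conclude that the primary analysis is not prespecified or that the 5% error is already lost. Knowing the arms is not the same as knowing the results, and inflation needs a choice actually driven by results. If that happened within the readings considered, the error would be about 7 to 8% instead of 5%. This is an upper bound for that set of readings on assumed inputs. The change is worth making because it is cheap; it does not call the design into question.

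**What to change.** Amend Randomization and masking so that the final analysis plan is approved and dated before any investigator is unmasked, with investigators masked until then. The monitoring board can remain the approving body.

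The document does not say whether investigators have been unmasked. If they have, report the date of unmasking beside the date of plan approval, and label as post hoc any primary-analysis choice made between the two, including the covariate set and the handling of recurrent infections.

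The cost is one sentence and a dated sign-off. Investigators may learn the arms somewhat later than now planned. No further data or staff are needed.
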